## Abstract

**Background:**

Despite the proven efficacy of antipsychotics in relapse prevention in schizophrenia and schizoaffective disorder, every third patient experiences a relapse within less than one year. Relapses can worsen psychosocial and treatment related outcomes and lead to substantial economic costs, primarily due to frequent and prolonged hospitalizations. The aim of this project is to evaluate a smartphone- and web-based digital solution for detecting early warning signs of schizophrenia and schizoaffective disorder to reduce relapses and subsequent hospitalizations.

**Methods:**

This randomized controlled trial compares the add-on use of a smartphone-based app for monitoring relapse warning signs in patients with schizophrenia and schizoaffective disorders (ICD-10 F20/F25) used within the routine psychiatric outpatient treatment against treatment as usual (TAU) without any further study-related intervention. Patients in the intervention group use the app for one year, fill in the weekly ten-item Early Warning Signs Questionnaire (EWSQ-10P) and obtain in-app feedback. Clinicians can access the symptom trajectory via a browser-accessible dashboard. If a threshold is exceeded in the inbuilt automatic algorithm, an alert is sent to both, the clinician and patient, enabling timely contact and, as part of a shared decision-making process, an optional adjustment of treatment decision. A total of 110 outpatients are recruited across eight study sites.

**Discussion:**

Continuous monitoring of early warning signs is expected to lead to behavioral changes and to decrease the necessity and duration of psychiatric hospital stays, thereby lowering healthcare costs. Additionally, the intervention could reduce symptom severity, alleviate medication adherence, shared decision-making, patient activation or quality of life. Qualitative data is collected to better understand patient needs and preferences regarding app usage and relapses. Insights gained from this study can be integrated into routine psychiatric care, improving the long-term treatment of patients with schizophrenia or schizoaffective disorder.

**Trial registration:**

German Clinical Trials Register (ID: DRKS00034991; registration date: 30.08.2024).

**Supplementary Information:**

The online version contains supplementary material available at 10.1007/s00406-025-02089-7.

## Introduction

Relapses occur frequently in patients with schizophrenia and schizoaffective disorder due to the chronic nature of these conditions [1–3]. Although a universally accepted definition of relapse in these disorders remains elusive, it is commonly characterized by psychiatric hospitalization or a measurable worsening of symptom severity [4–6]. Almost 40% of patients with schizophrenia and 28% of patients with an schizoaffective disorder require rehospitalization within twelve months after hospital discharge [7, 8]. Meta-analyses have shown that antipsychotics are more effective than placebo in relapse prevention. However, even with antipsychotic prophylaxis, 27% of patients experience a relapse within 10 months, whereas this figure is significantly higher at 61% under placebo [9, 10]. The evidence that relapses worsen disease progression and increase risk of treatment resistance is mixed [11, 12]. However, higher relapse rates are demonstrably associated with lower psychosocial outcomes such as unemployment, hopelessness or overall poorer quality of life [13], and patients often experience heightened anxiety about relapses [14, 15]. Above, associated costs are more than four times higher in relapsed schizophrenia patients than in non-relapsed patients [11]. Following the first two months after hospital discharge, the healthcare costs for patients with schizoaffective disorder are significantly higher than later on, mainly due to rehospitalizations and costs for medication [16]. Schizophrenia and schizoaffective disorder are both costly conditions, with the total systemic burden driven primarily by frequent and prolonged hospitalizations, as well as indirect costs such as unemployment and lost productivity [11, 17–20]. Developing strategies to reduce relapses is urgently needed and would substantially alleviate the disease burden for those affected, their families, and society.

Studies and guidelines unanimously emphasize the need to recognize early warning signs of relapse in schizophrenia, which have been shown to occur several weeks before a relapse [21–24]. They usually consist of non-specific symptoms such as sleep disturbances or fluctuations in affect, increasing disorganization of behavior or cognitive dysfunction [22, 25]. If early warning signs are recognized timely, not only by the clinician but also by patients and relatives, medication and other treatment measures can be adjusted, potentially reducing relapse rates [18, 26]. The ITAREPS program (Information Technology Aided Relapse Prevention Program in Schizophrenia) implemented a text message-based solution, where patients with schizophrenia weekly completed the 10-item Early Warning Signs Questionnaire (EWSQ-10P) on their phones [27]. A validated algorithm calculated the likelihood of relapse and alerted the clinician via text message when the risk was high, enabling timely intervention through medication adjustments or any other necessary measures. Using this approach, a randomized controlled trial showed that using the intervention in addition to routine treatment could reduce the hospitalizations by up to 60% compared to treatment as usual [28].

The present study aims to strengthen patient autonomy by actively involving patients with schizophrenia or schizoaffective disorder into a smartphone-based early warning system. Previous studies showed that shared-decision making tends to improve treatment satisfaction and potentially reduce rehospitalization rates [29, 30]. In contrast to the simplistic method of merely sending a text message to alert clinicians of an increased relapse risk, this study seeks to develop a digital solution that graphically displays the trajectory of early warning signs longitudinally on patientsˈ smartphones, making the information transparently accessible to both, patients and clinicians. We hypothesize that such an application will enhance transparency, encourage behavioral changes, increase the use of shared decision-making in clinician-patient communication, improve medication adherence and insight into their own likelihood of relapse and the trajectory of early warning signs. Ultimately, this approach is expected to reduce hospital readmissions, inpatient days, and psychiatric healthcare costs.

## Methods

### Trial design

The planned study (“IT-based relapse monitoring for schizophrenia”; acronym: ILIA) is a randomized-controlled (RCT), multicenter clinical trial evaluating the use of a smartphone- and web-based monitoring system for early warning signs of relapse integrated into standard clinical treatment, compared to treatment as usual (TAU) without digital monitoring. The study is conducted in outpatients with schizophrenia or schizoaffective disorders at 8 psychiatric hospitals in Munich, Augsburg and Berlin (Klinikum rechts der Isar, Ludwig-Maximilians-Universität (LMU) Klinikum, Isar-Amper-Klinikum München-Schwabing, München-Ost, Atriumhaus and Fürstenfeldbruck, Bezirkskrankenhaus Augsburg, Charité Universitätsmedizin Berlin). The inclusion is already possible at the end of an inpatient stay. The RCT is planned for 24 months, with the patients being recruited sequentially for 12 months. The intervention duration itself is 12 months. The protocol is registered in the German Clinical Trials Register (ID: DRKS00034991; registration date: 30.08.2024). An independent ethics committee reviewed and approved the research project (Technical University Munich, approval number: 2024-242-S-KK). The respective ethics committees of the participating clinics have followed the lead opinion of the ethics committee of the Technical University of Munich.

### Participants

We include participants 18 years and older with a diagnosis of schizophrenia or a schizoaffective disorder (ICD-10 F20/F25) who are currently in outpatient treatment. Participants can be at maximum markedly ill (CGI-S and PANSS-6 positive symptoms: delusions, conceptual disorganization and hallucinations ≤ 5) and should have had a relapse within the last two years prior to study inclusion. For this study, we defined relapse as a past hospitalization or a clinical increase in psychotic symptoms. The relapse inclusion criterion does not apply to patients whose initial disease onset occurred less than three years ago. Participants should be able to give their informed consent before the study starts. Participants must not be experiencing an acute exacerbation at the time of study inclusion, based on the judgment of the treating clinician. They further should not have any other cognitive or physical impairments that prevent adequate study participation.

### The smartphone-based monitoring app and the digital clinic portal for feedback

In the ILIA-study we collaborate and license the products of Mindpax.me, a Czech-based company founded in 2015, emerged from the intersection of mental health research and digital innovation, aiming to improve the monitoring and management of mental health disorders through data-driven wearable technologies and advanced analytics. Mindpax.me offers continuous, long-term disease monitoring systems for patients with psychiatric disorders to provide psychoeducational suggestions to increase their competency of self-management, prevent relapse and increase the duration of remissions [31].

#### The early-warning-signs questionnaire (EWSQ-10P)

During the 12-month intervention period, the participants in the intervention group enter ten possible early warning signs according to the EWSQ-10P [27] in an app on their own smartphones on a weekly basis. The EWSQ-10P is a scale used to assess the following early warning signs: Sleep disturbances, loss of appetite, concentration difficulties, increased anxiety, paranoia, inner restlessness/irritability, loss of energy, difficulty solving everyday problems and acoustic hallucinations. The 10th item of the EWSQ-10P is a personalized early warning sign and can be set and changed individually by the patient during the course of the study. The EWSQ-10P assesses the change in symptomatology compared to the previous week, i.e., the last questionnaire. The EWSQ-10P has adequate internal consistency and convergent validity [27]. We build upon the original ITAREPS algorithm for generating alerts for impending relapse (access to more than 600 patient years). If the ITAREPS algorithm, using total score and sub-scores of the current, as well as previous EWSQ-10P exceeds a certain threshold, a warning signal is issued, notifying both, patients and clinicians. Upon the warning, the patient enters an alert state and the EWSQ-10P is requested twice a week. The alert algorithm uses a setting that is more sensitive to further deterioration of the clinical status and increased relapse risk.

#### Functionalities of the sigma.me app

The ˈSigma.meˈ App runs on iOS and Android systems. Figure 1 shows the interface of the ˈSigma.meˈ App that is used in the intervention group. From left to right, the home screen shows the notification to complete an upcoming EWSQ-10P questionnaire, as well as the health status overview of the past weeks. The second interface of Fig. 1 shows an example question from the EWSQ-10P. Answers are shaded in colour depending on the answer option to ease the filling out procedure for the patients. This design was adopted based on a participatory preliminary study phase, in which patient representatives gave feedback on the user interface in focus groups. The next two interfaces show the graphical feedback on the home screen depending on varying answers in the questionnaire and the respective change in health status. Participants can also insert any change in medication in-take or life events (e.g. challenges at work or within relationships) and mark those events as a trigger. This allows the patient to indicate events that may worsen their condition and avoid them in the future. A long-term overview screen allows the patient to see the course of their relapse risk and quickly recognize the relationships between events, medication changes, and their mental state. Clicking on “symptom overview” directs participants to the very right interface depicted in Fig. 1. Here, patients can inquire about the detailed history of their health, broken down into the ten early warning signs.

**Fig. 1 Fig1:**
[figure not shown]
Interface of the Sigma.me App

Graphical depictions of weather icons within the smartphone app represent participants´ current health status based on questionnaire responses (Figs. 1 and 2). The various icons and their meanings are as follows: The smiling sun indicates no deterioration based on the questionnaire responses, suggesting that the patient is stable. The sun with a few clouds reflects a slight deterioration, but not enough to trigger an alarm period. The rain cloud represents either a threshold exceedance, triggering the alarm period, or a slight but not significant deterioration during an ongoing alarm period. The thunderstorm clouds signify a significant deterioration during the current alarm period, prompting the three-week alarm period to restart.

In an alert state, patients are required to complete the EWSQ-10P twice a week for three weeks and an orange shaded banner on the home screen reminds the patient of the alert status. The alert period lasts for a minimum of three weeks. Its extension depends on further deterioration of the patient’s condition. If the patient’s condition does not worsen further, the alert period automatically ends and patients resume completing the questionnaire weekly. The change in status can be seen by a shift in the weather icon from rain to sunshine. The wording and clarity of these icons were participatory reviewed and adjusted in focus groups during the preliminary study phase in collaboration with patient representatives to ensure their comprehensibility and effectiveness.

**Fig. 2 Fig2:**
[figure not shown]
Info-Button of the home screen that explain depiction of health status in the form of weather icons

#### Digital clinic portal for clinicians

The information from the app is sent to and processed on a secure server. Clinicians can view the course of the early warning signs at any time through access to a digital clinic portal via a web-application. Figure 3 shows the home screen of the digital clinic portal, with an overview of included patients, the date they last completed the ESWQ-10P and their current health status. Clicking on the button “View” takes clinicians to the interface depicted in Fig. 4. Similar to within the app, a dotted line shows the course of relapse risk of the respective patient during the past weeks. The colour of the dots helps to indicate the change in status, i.e., green indicates no worsening. Clicking on the dots takes clinicians to a detailed table showing the changes in the ten early warning signs compared to the previous week.

**Fig. 3 Fig3:**
[figure not shown]
Home screen in the digital clinic portal with patient overview

**Fig. 4 Fig4:**
[figure not shown]
Overview of the digital clinic portal: Single patient status dashboard (overall risk of falling in relapse)

Clinicians are notified via email in four cases: A patient (1) enters the alert state, (2) extends the alert state, (3) exits the alert state or (4) missed a questionnaire twice in a row. The latter scenario is called “silent patient” and could constitute another early warning sign of relapse. In all cases, except for a patient exiting an alert period, the patient and clinician should promptly get in touch, e.g. via phone, to assess the patientˈ current (mental) health status. This is a shared responsibility of both, the patient and the clinician. As part of a shared decision-making process, the next treatment steps should be decided in a participatory manner. The action to be taken in response to an alert is not prescribed by the study and is left entirely to the shared decision-making between the clinician and the patient. For example, they may decide to provide psychoeducation, to improve sleep hygiene, issue a sick note, possibly adjust antipsychotic medication, or jointly deciding that no action is needed.

After the joint conversation about an (extended) alarm, clinicians must document the measures decided upon. This happens within the digital clinic portal, using a “Notes” function embedded in every patient profile. Additionally, a study team member will review the measures implemented in response to an alert at the next study visit.

### Baseline set-up and technical support for the digital intervention

Before the study starts, clinicians from participating centers undergo multiple introductory sessions, including a final one-on-one on-boarding session, in which the account in the digital clinic portal is set up together study team members. For patients, after baseline assessment and randomization, participants of the intervention group download the Sigma.me app on their smartphone. Study staff assists patients with the set-up and registration procedure. Patients receive a pseudonymized study email as their user name. The study team acts as a first level helpline for patients and clinicians, e.g. in case of lost passwords or problems with the app and portal usage.

Built-in help buttons assist patients to navigate the app, when no assistance is available. Help-buttons explain the weather icons (Fig. 2), how the EWSQ-10P questionnaire assesses changes compared to the previous week, and how to add new symptoms or change the personalized early warning sign.

Moreover, printed fact sheets are handed to patients and clinicians (see Multimedia Appendix 1). Patients can refer to these sheets to review their log-in details, while clinicians can use them to review the study procedure in case of an alert period. These fact sheets serve as quick reference guides for navigating the respective interfaces and understanding their functionalities. The fact sheets also provide contact details for technical support, ensuring that patients and clinicians can contact the study team at any time and have the resources to use the applications effectively. A regular newsletter helps to keep participating clinicians up-to-date and bimonthly video conference calls are offered to clarify open questions, help with technical issues or share experiences on implementation barriers or best-practice examples.

### Sample size and recruitment

We aim for a sample size of *N* = 110 patients recruited from *n* = 8 clinics. The sample size calculation is based on the outcome “number of patients requiring inpatient psychiatric admission within one year.” A randomized pilot study using a simple text message-based solution to monitor early warning signs showed large effect sizes [28]. Since we expect the pilot study effect to be inflated and cluster effects present in our study, we opt for a considerable smaller, but still moderate effect (w = 0.30) for sample size calculation. Using a chi-squared test without cluster effects, a group size of 44 patients per group provides a power of 80% to detect a population effect of w = 0.30 with a two-sided Type I error rate of 5%. Assuming a dropout rate of approximately 20% [28], 110 patients need to be recruited. An approximately equal distribution across the eight centers is planned.

Identification of suitable patients and recruitment is supported by local clinicians in the clinics. Flyers and posters at local study sites support the recruiting process. Additionally, patients are recruited at external centers, such as counseling centers, assisted living groups, or self-help groups. To ensure a comprehensive recruitment process, social media is also included. Experienced study staff at the lead center, Klinikum rechts der Isar in Munich, and the Berlin study center are responsible for enrolling participants in the study, including obtaining informed consent. External patients are getting affiliated with one of the participating clinics for the duration of the study. They can choose to fully transfer to our outpatient clinics during the study period or remain with their local doctor while simultaneously attending the participating outpatient clinic.

A study phone will be provided for patients who do not own a private smartphone but still possess basic digital skills, such as using a PC or tablet, and having an internet connection at home. However, these cases are reviewed individually and thoroughly to ensure that no bias arises.

### Randomization and blinding

Individual randomization (1:1) ensures a balanced distribution of participants and their treating clinicians between the intervention and control groups across all centers (Fig. 5). Randomization is automatically conducted after obtaining informed consent and prior to the baseline assessment using the randomization tool in RedCap, a secure web-based electronic data capture tool hosted at Yale University, designed for data collection and management in research studies [32, 33]. Due to the nature of the intervention, blinding is not possible.

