**Fig. 5 Fig5:**
[figure not shown]
Study flow diagram. Randomization before T0. Five study visits every 3 months for 12-month study duration. Qualitative data collection with a representative subsample of study participants

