### Outcomes

#### Baseline parameters

At baseline (T0), sociodemographic data (age, sex, nationality and language, educational background, family and occupation status) and history of illness (ICD-10 diagnoses, duration of illness, number of previous hospitalizations, previously prescribed medications, substance abuse) is collected via patient and clinician-rated questionnaires (Table 1).

**Table 1 Tab1:** Planned timepoints and data collection

Scale/item	Visit 0 (T0)	Visit 1 (T3)	Visit 2 (T6)	Visit 3 (T9)	Visit 4 (T12)
	Baseline	Week 13 +/- 3 weeks	Week 26 +/- 3 weeks	Week 39 +/- 3 weeks	Week 52 +/- 3 weeks
Written informed consent^a^	X^b^				
Screening/Assessment of inclusion/exclusion criteria^c^	✓^d^				
Sociodemographic characteristics	X				
Psychiatric diagnose(s) after ICD plus code	✓				
Change of psychiatric diagnosis(es)		✓	✓	✓	✓
Duration since first diagnosis	✓				
Number of previous episodes until now	✓				
Psychiatric comorbidities	✓				
Number of hospitalizations until now	✓				
Hospitalization days due to psychiatric illness in the past two years	✓				
Substance abuse	X	X	X	X	X
Alcohol abuse	X				
Smoking	X				
Currently psychiatric medication(s)	✓	✓	✓	✓	✓
Change and date in psychiatric medication(s)		✓	✓	✓	✓
Current other measures: e.g., psychotherapy, group therapy	✓	✓	✓	✓	✓
Rehospitalization (yes/no) and brief summary of admission reasons		✓	✓	✓	✓
Days in hospital since last study visit		✓	✓	✓	✓
Time to hospitalization		✓	✓	✓	✓
eHeals-g	X				
Questionnaire on prospective acceptance of eHealth	X and ✓				
Alarms since last study visit		✓	✓	✓	✓
Measures taken, if any, following the alarm		✓	✓	✓	✓
EWSQ-10P (control group only)	X	X	X	X	X
SDMQ-9	X	X	X	X	X
PAM13	X	X	X	X	X
ZUF-8	X	X	X	X	X
15-STARS	X	X	X	X	X
Question on Adherence	X	X	X	X	X
CGI-S/C	✓	✓	✓	✓	✓
PANSS-6	✓	✓	✓	✓	✓
FORSE	X	X	X	X	X
EuroHisQoL	X	X	X	X	X
WHODAS 2.0	X		X		X
SOFAS	✓	✓	✓	✓	✓
ANTISIDES	X				X
UKU-SERS self-rating	X				X
Mannheimer Resource Consumption Module	X				X
Reason for Dropout^e, f^ (if applicable)		✓	✓	✓	✓

^a^Written informed consent must be obtained at Baseline Visit 0 before data collection starts

^b^A X indicates the scale is patient-rated

^c^Screening can be done at Visit − 1 before Baseline or on the same day of Baseline at Visit 0

^d^A ✓ indicates the scale is clinician-rated

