#### Secondary outcomes

To complement our primary outcome of hospitalizations, we assess whether the intervention reduces the days spent in hospital and the time to hospitalization at three month-interval study visits (T0, T3, T6, T9, T12).

At every study visit (T0 – T12) we assess whether the app promotes more shared decision-making in the course of treatment (Shared Decision Making Questionnaire, SDM-Q9) [36], changes fear of relapse (Fear of Recurrence Scale Questionnaire, FORSE) [15], increases patient satisfaction (Patient Satisfaction Questionnaire, ZUF-8) [37] and patient activation (Patient Activation Measure, PAM-13) [38], and thus potentially improving medication adherence (Screening Tool for AdheRence to medicineS, 15-STARS) [39].

To better understand whether the intervention improves symptomatology, we use the 6-item version of the Positive and Negative Syndrome Scale (PANSS-6) [40] and the Clinical Global Impression Severity/Improvement (CGI-S/C) [41]. All three scales are rated by the clinician after patient study visit (T0 – T12). The clinician-rated Social and Occupational Functioning Assessment Scale (SOFAS) [42] is also assessed at the same timepoints.

Changes in Quality of Live (QoL) are assessed via the patient-rated EUROHIS-QOL [43] every three months. Patients report changes in social/global functioning via the WHODAS 12-item scale [44] at T0, T6 and T12. We evaluate the presence and severity of medication side effects using the Udvalg for kliniske undersøgelser scale (UKU-SERS) [45] and patient-reported antipsychotic and antidepressant side-effect scale (ANTISIDES). Those two measures are assessed at baseline (T0) and after study completion (T12).

To evaluate whether the implementation of a smartphone-based relapse monitoring smartphone is cost-effective from a pharma-economical perspective, we use the Mannheimer Resource Consumption Module Questionnaire at T0 and T12 [46].

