### Data analysis

#### Analysis of quantitative data

The primary outcome parameter (psychiatric hospital admission) will be analyzed using a mixed model (logistic regression) with random intercepts for wards. Exploratory analyses of secondary outcome parameters will also be conducted: Differences in the time to hospitalization and simple relapses will be analyzed using a Kaplan-Meier curve and the log-rank test or within a generalized linear model framework (“Piecewise Exponential Model”). Additionally, we want to explore whether the effect of treatment is related with eHealth literacy and the acceptance of digital interventions with a subgroup analysis. Other secondary outcome parameters will be analyzed using mixed-effect regressions with random intercept for wards (logistic regressions if binary and linear regressions if continuous). If there are repeated measures available, this will be investigated within a multilevel framework, with random intercepts for subject and random slopes for time, if applicable.

Following the ITT principle, people that withdraw from the study (missing follow-up) need to be accounted for in the analysis. To deal with missingness, the primary analysis will adjust for baseline PANSS-6 score and age, since we expect these variables to be related to missingness. We expect an adjusted analysis to be the most efficient way to account for missing data in our experiment, mostly because of the binary outcome and the structure of missingness that is common in RCTs [51, 52]. The considerations for missing data will be subject to a sensitivity analysis. For this, missing values will be imputed with MICE (Multiple Imputation for Chained Equations) under a Missing at Random assumption. Imputation is an attractive alternative to our primary analysis, since there are many possible auxiliary variables measured at baseline that are not incorporated into the adjusted primary analysis. Additionally, in the case that there is a lot of dropout of similar structure (Reasons for Dropout), a sensitivity analysis under a MNAR assumption (pattern-mixture models) will be conducted.

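### Randomisation precedes the T0 assessment in an open-label trial, so the PANSS-6 covariate and the planned moderators are measured after allocation, with the arm probably known

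*Protocol article*

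**What the plan says.** All references are to the protocol article.

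- **Order of procedures.** Randomization and blinding: "Randomization is automatically conducted after obtaining informed consent and prior to the baseline assessment". The Fig. 5 caption repeats it: "Randomization before T0". Baseline set-up and technical support words it differently: "after baseline assessment and randomization, participants of the intervention group download the Sigma.me app on their smartphone".
- **Blinding.** Randomization and blinding: "Due to the nature of the intervention, blinding is not possible". No section says that the allocation is held back until T0 is finished.
- **A T0 form that depends on the arm.** Table 1 has a row labelled "EWSQ-10P (control group only") that is marked at T0 as well as at the later visits.
- **Raters.** Of PANSS-6 and the two CGI scales, Secondary outcomes says: "All three scales are rated by the clinician after patient study visit". T0 is included.
- **Use of the T0 values.** Analysis of quantitative data: "the primary analysis will adjust for baseline PANSS-6 score and age". The same section plans to "explore whether the effect of treatment is related with eHealth literacy and the acceptance of digital interventions with a subgroup analysis". Table 1 collects both of these variables at T0, acceptance from the patient and the clinician.
- **Eligibility.** Participants sets a ceiling of 5 on CGI-S and the PANSS-6 positive items. Table 1 footnote c allows screening at a Visit −1 or on the day of Visit 0. Footnote a places written consent at Visit 0, ahead of any data collection.

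**The concern.** A baseline covariate is safe to adjust for because allocation cannot have affected it. If it is recorded after an open allocation, that guarantee is lost. A rater or patient who knows the arm may score differently, and any systematic difference in the recorded covariate passes into the adjusted treatment effect.

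Four uses of T0 data are exposed:

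1. PANSS-6 as a covariate in the primary logistic model. Age, the other covariate, cannot be affected.
2. The T0 values of subjective scales such as SDM-Q9, ZUF-8, PAM-13 and FORSE, which are the starting point of the repeated-measures analyses.
3. The two moderators. Asking about prospective acceptance of eHealth just after someone has been given or refused the app is the clearest case in which the answer may reflect the allocation.
4. The auxiliary variables for the multiple-imputation sensitivity analysis. The article describes them as measured at baseline, but under the stated order they too are collected after allocation.

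There is also a completeness problem. Someone who withdraws after learning the arm but before T0 is randomised without a PANSS-6 value. That patient cannot enter the adjusted primary model without imputation, although the analysis is meant to follow the ITT principle.

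**Working it through.** **Step 1. The order, side by side.**

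| Place | What it implies |
|---|---|
| Randomization and blinding | consent, then randomisation, then baseline |
| Fig. 5 caption | randomisation, then T0 |
| Table 1, EWSQ-10P row | the arm must be known when the T0 forms are given |
| Baseline set-up | baseline and randomisation both precede the app download; baseline is named first |

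Two places state the order outright and a third is consistent with it. The fourth suggests another order through its word sequence, but it fixes only that both steps come before the download.

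**Step 2. Eligibility.** With screening at Visit −1, the ratings precede randomisation. With screening on the day of Visit 0, nothing places the eligibility check before randomisation. Arm-aware eligibility ratings are therefore possible but not shown. Footnotes a and c also fit poorly together: consent at Visit 0 is to precede data collection, yet screening may take place earlier.

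**Step 3. The plan's own figure.** For a 1-df chi-squared test, N = (z₀.₉₇₅ + z₀.₈₀)² / w² = (1.960 + 0.842)² / 0.30² = 87.2, so 88, or 44 per group. Power at 88 is 80.4%. With 20% dropout, 88 / 0.8 = 110. The stated sample size reproduces, and moving randomisation after T0 does not change it.

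**Step 4. Possible size of the bias.** The documents give neither the PANSS-6 slope nor a rating shift, so both are assumptions. If recorded PANSS-6 is d SD higher in the app arm only because the arm is known, and the log-odds of admission rise by b per SD, the adjusted treatment log-OR moves by about −b × d.

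- b = 0.5, d = 0.2: 0.5 × 0.2 = 0.10; exp(0.10) = 1.11
- b = 0.5, d = 0.4: 0.5 × 0.4 = 0.20; exp(0.20) = 1.22

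If the shift goes the other way, the sign reverses.

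**Step 5. Simulation with no true treatment effect.** R is the assumed odds ratio of admission per SD of true PANSS-6 (b = 0.5 corresponds to R = 1.65). Admission is about 35%.

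| R | Adjusted OR, d = 0.1 | d = 0.2 | d = 0.3 | d = 0.5 |
|---|---|---|---|---|
| 1.3 | 0.98 | 0.95 | 0.92 | 0.88 |
| 1.5 | 0.96 | 0.92 | 0.89 | 0.81 |
| 2.0 | 0.93 | 0.86 | 0.82 | 0.71 |

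These agree closely with R^(−d). The type I error with 44 per arm (4,000 runs, Monte Carlo standard error about 0.3 percentage points) was:

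| R | d = 0 | d = 0.3 | d = 0.5 |
|---|---|---|---|
| 1.5 | 5.5% | 6.5% | 6.8% |
| 2.0 | 5.2% | 7.0% | 10.3% |

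**Step 6. Relative to the planned effect.** Take a control admission rate of 40% as an assumption, from the Introduction's figure of almost 40% for schizophrenia. Then w = 0.30 implies about 13.4% in the app arm and a log-OR of 1.46 in absolute size, so a shift of 0.10 to 0.20 is 7% to 14% of it. With 28% (the schizoaffective figure), the app-arm rate is about 5.6%, the log-OR 1.89, and the share 5% to 11%.

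**The case against.** The strongest reply is that no harm is shown. At T0 nobody has used the app, so only expectation could move the ratings. The admission outcome does not use the baseline scale, the direction of any shift is unknown, and the assumed bias is small next to the planned effect. The type I error exceeds 10% only in the most extreme assumed case. The secondary and moderator analyses are labelled exploratory. All of this stands, and it limits the claim to a risk. It does not rescue the order itself: an analysis plan cannot turn a measurement taken after allocation into a baseline one, and preventing the problem costs almost nothing.

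Several stronger readings are tempting and are not supported:

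- **That the set-up section states the opposite order.** It only puts both steps before the app download. The wording needs aligning; it is not a flat contradiction.
- **That eligibility is rated with the arm known, so that post-randomisation exclusions follow.** Visit −1 screening is allowed, and no order is given for same-day screening.
- **That the treating clinician rates PANSS-6.** Secondary outcomes says only that a clinician does. The treating clinician is named in Participants for the judgement on acute exacerbation.
- **That change-from-baseline results are distorted.** No change-score analysis is specified; the plan is mixed-effect regression.

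There is also a fair objection to simply dropping PANSS-6 from a sensitivity analysis: the plan includes it because it is expected to relate to missingness.

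**Conclusion.** The concern holds in a limited form. The stated order makes the primary model's PANSS-6 covariate, the T0 subjective scales and both moderators post-randomisation measurements in an unblinded trial. Table 1 implies that the arm is known when they are taken. It also allows a randomised patient to have no value for the primary covariate.

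That ratings actually differ by arm is a risk and not a documented fact. The shift of 0.10 to 0.20 in the log-OR rests wholly on the assumed slope of 0.5 per SD and rating shift of 0.2 to 0.4 SD, and its sign is unknown. Confidence is high on the order of procedures and low on the amount of bias. The change is worth making because the exposure reaches the primary analysis, grows with each patient enrolled under this order, and cannot be undone afterwards for those patients.

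**What to change.** 1. State one order in Randomization and blinding, Baseline set-up and technical support, Fig. 5 and Table 1: consent; eligibility check; all patient- and clinician-rated T0 forms completed and locked in REDCap; then release of the allocation. Reconcile Table 1 footnotes a and c on consent and screening at the same time. The controls-only EWSQ-10P row at T0 needs attention too, since under this order the arm is not yet known when the T0 forms are filled in.
2. Flag patients already randomised before T0. Add a sensitivity analysis of the primary outcome that replaces T0 PANSS-6, adjusting for age and psychiatric hospital days in the past two years. Hospital days are also recorded at T0, so check them against records. State that leaving out PANSS-6 weakens the missing-data adjustment, and present the result beside the planned analysis, not in place of it.

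Cost: a change to the REDCap workflow, a short amendment and one extra analysis. Clinician ratings must be finished before allocation, so app onboarding may be slightly delayed. The sample size of 110 stays as it is.
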